### Setting and recruitment

Women are recruited in Auckland, NZ using media articles and advertising (e.g. in newspapers, magazines, on websites and radio interviews). Posters and flyers are used in a variety of venues including local crèches, primary schools, secondary schools, local businesses and events (e.g. gym’s, libraries, and sport events). The study is also advertised using social media (e.g. Facebook, twitter) and via emailing lists (e.g. Massey University staff, student, and previous research participant databases). Potential participants are directed to a study website for further information and to register their interest in the study. For the Māori and Pacific cohorts, recruitment strategies were adapted to be culturally appropriate. A more personal approach with face-to-face contact by community liaisons, were used to recruit women. Screening (see Stage 1 under procedures) was conducted within the respective communities and special assistance was provided for participants to travel to Massey University for further data collection (Stage 2).

### Procedures

The study follows a three-staged approach that involves screening (Stage 1), on-site assessments (Stage 2), and at-home assessments (Stage 3) (Figure 1).

#### Screening (stage 1)

Women who register interest are provided with an information sheet and asked to complete a consent form and the screening questionnaire. If all the inclusion and exclusion criteria assessed using the screening questionnaire is met, BMI (calculated using height and weight) and BF% (assessed using bioelectrical impedance (BIA)) are used for preliminary categorisation into the body composition profile groups (described above). The body composition screening is done in person and either at the Human Nutrition Research Unit, Albany campus, Massey University, or off-site.

#### Assessments (stages 2 and 3)

Participants recruited in stage 1 are invited to the research unit within 14 days of the start of their last menstrual period (the follicular phase) for testing to avoid the confounding effect of menstrual cycle hormones on taste perception, energy intake and energy expenditure (Davidsen et al. 2007).

Stage 2 of testing involves measurements of anthropometry, body composition, metabolic health, dietary intake, taste perception, and eating behaviour, which are described in detail below.

Stage 3 of assessment is completed at home over a seven day period. Participants wear accelerometers and keep a physical activity diary to assess physical and sedentary activity objectively in real life. At the end of the seven days, participants complete the RPAQ and the dietary diversity questionnaire (DDQ) (see Figure 1).

### Measures

The chosen measures and/or methods used for the various assessments in stages 1, 2 and 3 are listed in Table 1.

**Table 1 Tab1:** **Measures and methods**

**Domain**	**Measures / methods**	**Reference**	**Equipment**	**Concept captured**
Body composition: anthropometry.	Anthropometric measurements (height, weight, circumferences) using ISAK protocol and standards.	(NHLBI Obesity Education Initiative Expert Panel on the Identification Evaluation and Treatment of Overweight and Obesity in Adults 1998)	Stadiometer, Lufkin tape.	Body composition.
				- Profile in terms of BMI (weight, height)
				- Risk in terms of circumferences and ratios (waist, hip, height).
Body composition profile – fat and lean mass.	-	(Ling et al. 2011)	Bioelectrical Impedance (BIA) (InBody230, Biospace Co. Ltd, Seoul).	Body composition - (fat and lean mass).
				- total
	-	(Noreen and Lemon 2006; Wingfield et al. 2014)	Air displacement Plethysmography (BodPod) (2007A, Life Measurement Inc, Concord, Ca., using software V4.2+ as supplied by the manufacturer).	Body composition - (fat and lean mass).
				- total
	-	(Boneva-Asiova and Boyanov 2008)	Dual XRay Absorptiometry (DXA) (Hologic QDR Discovery A, Hologic Inc, Bedford, MA. with APEX V. 3.2 software.	Body composition - (fat and lean mass).
				- total
				- regional
Metabolic health – biomarkers.	Analysis will be conducted by fully accredited laboratory with IANZ to the ISO 15189.	-	Blood sampling to capture plasma glucose, total cholesterol, triacylglyceride, HDL-cholesterol, LDL-cholesterol, insulin, serum hs-CRP, Il6, TNF-alpha, HbA1C, Leptin, Ghrelin.	Biomarkers related to metabolic health (lipid profile, glucose control, inflammation, hormonal control).
Metabolic health – blood pressure.	-	(Ogedegbe and Pickering 2010)	Blood pressure measurement Riester Ri-Chamion N digital blood pressure monitor, using one of two arm cuff sizes (22-32 cm or 32-48 cm).	Blood pressure related to metabolic health.
Metabolic health – gene expression	-	(Russell et al. 2012; Zacharewicz et al. 2014 )	miRNA - use specific primer and probes sets as per the manufacturer’s instructions (Applied Biosystems, Carlsbad, USA) using an MX3000p thermal cycler system. miRNA species will be measured using published techniques.	MiRNA related to energy expenditure.
Diet Quality	Food Frequency Questionnaire (FFQ)	(Ministry of Health NZ 1997; McNaughton 2011; Mishra et al. 2010)	Analysis using Foodworks7 2010 (Xyris Software (Australia) Pty Ltd, Queensland, Australia).	Dietary adequacy
				- energy intake
				- nutrient intake
				Patterns of food and nutrient intake.
Diet Quality	Eating Habits Questionnaire	Developed in this study	-	Dietary habits
				- eating habits
				- meal distribution
				- food choices.
Dietary Variety	Dietary Diversity Questionnaire (DDQ)	Developed in this study; mostly based on foods in the FFQ	-	Dietary diversity
				Food variety.
Dietary Behaviour	Three Factor Eating Questionnaire (TFEQ)	(Stunkard and Messick 1985)	-	Dietary behaviour
				- Restraint,
				- Disinhibition,
				- Hunger.
Physical Activity patterns	-	(Pescatello and American College of Sports Medicine 2014)	WGT3X Actigraph	Objective real life physical activity
				Physical activity expenditure
				- sedentary activities
				- intensity of activity.
	Physical Activity diary	-	-	Self-reported accelerometer non-wear time
				Self-reported intentional exercise
				– time
				- duration
				- type
				- intensity.
Physical Activity behaviour	Recent Physical Activity Questionnaire (RPAQ)	(Besson et al. 2010)	-	Self-reported physical activities
				- sedentary activities
				- time
				- intensity.
Taste perception, intensity, and hedonic preference	-	(Lim et al. 2008; Bartoshuk et al. 2004)	Rate intensity and hedonic preference of sweet and fat taste on a gLMS.	Sweet and fat taste sensitivity and preference.

#### Body composition assessment

Anthropometric measurements include weight, height, waist and hip circumferences using the International Society for the Advancement of Kinanthropometry (ISAK) protocol (Marfell-Jones et al. 2006). Waist-to-hip ratio, waist-to-height ratio and BMI will be derived from these measures and will be used to assess body composition in terms of obesity along with associated disease risk (NHLBI Obesity Education Initiative Expert Panel on the Identification Evaluation and Treatment of Overweight and Obesity in Adults 1998). Fat and lean mass are assessed using BIA (Boneva-Asiova and Boyanov 2008; Ling et al. 2011) for screening and preliminary categorisation into profile groups, and air displacement plethysmography (ADP) (using thoracic gas volume method) for final categorisation (Wingfield et al. 2014; Noreen and Lemon 2006), as well as DXA measurements for regional body composition (Boneva-Asiova and Boyanov 2008).

#### Metabolic health assessment

After an overnight fast (no food or beverages, excluding water for 12 hours prior to phlebotomy), blood samples are obtained by registered phlebotomists between 7.00 and 10.00 am and prior to sensory testing. Serum and plasma samples (ethylene diamine tetraacetic acid (EDTA) and heparin) are collected and processed in accordance with pathology laboratory protocols. All samples are frozen in separate aliquots in Eppendorf tubes and stored at −80°C until analysis. Analysis will be carried out by a fully accredited (with IANZ to the ISO 15189) laboratory or by qualified laboratory technicians upon completion of data collection. Biomarkers that will be analysed include plasma levels of glucose, total cholesterol, triglycerides, HDL-C, LDL-C, insulin, leptin, serum hs-CRP, Il-6 and TNF-alpha using commercially available kits or using routine enzymatic assays as published by our team (van Langenberg et al. 2014; Smith et al. 2012). The analyses will be performed using either a Biotek Synergy 2 Plate Reader (Millennium Science, Balwyn, Vic) or a Bioplex 200 plate reader (BioRad Hercules CA) depending on the required assay.

Selected miRNA species to assess metabolic disease risk and to explore energy expenditure and storage will be measured as published by our group (Russell et al. 2012; Güller and Russell 2010; Russell et al. 2013; Zacharewicz et al. 2014). For miRNA analysis, extracted RNA will be reverse transcribed using target specific primers followed by qPCR using target specific probes as published routinely by our group. All qPCR analysis will be performed using the Stratagene MX3000p thermocycler (Stratagene, La Jolla, CA); miRNA results will be normalized to RNA input and log transformed if not normally distributed.

Resting blood pressure measurements are taken whilst sitting, following a 10 minute resting period after taste perception assessments. For blood pressure measurements, an arm cuff is attached to the arm that has not been used for the venepuncture and three measurements are taken consecutively in one minute intervals (Ogedegbe and Pickering 2010).

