**Methods/Design:**

A cross-sectional design to investigate 675 NZ European, Māori, and Pacific women aged 16–45 years. Women are classified into three main body fat profiles (*n* = 225 per ethnicity; *n* = 75 per body fat profile): 1) normal BMI, normal body fat percentage (BF%); 2) normal BMI, high BF%; 3) high BMI, high BF%. Regional body composition, biomarkers of metabolic disease risk (i.e. fasting insulin, glucose, HbA1c, lipids), inflammation (i.e. IL-6, TNF-alpha, hs-CRP), associations between lifestyle factors (i.e. dietary intake, physical activity, taste perceptions) and microRNA expression will be investigated.

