### Participants and sample size

Study participants are adult NZ women from three ethnic groups (NZ European, Māori, and Pacific Island). A total sample size of 225 women per ethnic group, consisting of 75 per profile group, will provide 80% power at significance levels of p < 0.05 to detect a medium effect size *f* of 0.25 (G*Power 3.1.2) for comparing the “hidden fat” profile with the other two body composition profiles (“normal fat” and “apparent fat”) regarding metabolic disease risk markers, dietary and physical activity patterns, and miRNA expression levels.

The medium effect size is relevant to all variables, and encompasses a variety of scenarios, as we wish to be able to explore how metabolic profile changes with body composition. For example, if the three groups have equally spaced means (μ - Δ, μ, μ + Δ), the difference in means will be detected with 80% power when Δ = 0.31 x σ, where σ is the within group standard deviation. For cholesterol, where preliminary data suggests σ = 0.98 mmol/L, we have 80% power to detect the difference when Δ = 0.30 mmol/L. Alternately, if two groups have the same mean μ and the third has mean μ + Δ, 80% power is achieved when Δ > 0.53 x σ, or 0.52 mmol/L in the case of cholesterol. A Δ = 0.30 – 0.52 mmol/L is estimated to be associated with a 9 – 15% lower relative risk of coronary heart disease (CHD)-related mortality (Gould et al. 2007). For HDL-C where preliminary data suggests σ = 0.38 mmol/L we have 80% power to detect a difference when Δ = 0.12 – 0.20 mmol/L. Every 0.1 mmol/L increase in HDL-C has been suggested to reduce CHD risk by between 8 – 15% (Gordon et al. 1989; Turner et al. 1998). For TG where preliminary data suggests σ = 0.45 mmol/L we have 80% power to detect a difference when Δ = 0.14 – 0.24 mmol/L. Studies in women showed a 1 mmol/L increase in TG was associated with 37% increase in risk of CVD (after adjustment for HDL-C and other risk factors)(Austin et al. 1998); Δ of 0.14 – 0.24 is thus estimated to be associated with 5.2 – 9% difference in CVD risk.

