### Data handling and statistical analysis

Statistical analysis will be performed using IBM SPSS statistics (IBM Corporation, New York, USA). Descriptive statistics will be used to describe the baseline population using mean (standard deviation), median (25, 75 percentile) or frequencies summary statistics. Normality of distribution will be evaluated using the Kolmogorov-Smirnov test and examining normality plots. Non-normally distributed variables will be transformed into approximately normal distributions by logarithmic transformations and again tested for normality. Primary statistical analyses will involve ANOVA tests with post-hoc analysis and Bonferoni adjustments comparing body composition profile groups regarding metabolic disease risk markers and dietary and physical activity patterns and miRNA levels; multiple logistic regression analysis to determine odds ratios of having a “hidden body fat” profile based on dietary and physical activity patterns; and, separately, miRNA expression levels. Principal components analysis will be performed on the miRNA data using the PCP directive in GenStat to identify linear combinations of the miRNAs that account for most of the variation between individuals (Zacharewicz et al. 2014); and Pearson correlations to determine correlation coefficients between dietary and physical activity patterns and miRNA expression profiles. A p-value of <0.05 will be considered significant.

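### Logging miRNAs only when they look non-normal can put a mix of raw and log scales into the principal components analysis; one pre-set log scale and a correlation matrix would remove the risk

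*Protocol article*

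**What the plan says.** Metabolic health assessment gives the rule for the miRNA measurements: "miRNA results will be normalized to RNA input and log transformed if not normally distributed".

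Data handling and statistical analysis repeats it for variables in general: "Non-normally distributed variables will be transformed into approximately normal distributions by logarithmic transformations and again tested for normality". Normality is judged by a test together with plots: "Normality of distribution will be evaluated using the Kolmogorov-Smirnov test and examining normality plots".

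The same section then states: "Principal components analysis will be performed on the miRNA data using the PCP directive in GenStat". The aim is to "identify linear combinations of the miRNAs that account for most of the variation between individuals". The section also plans "Pearson correlations to determine correlation coefficients between dietary and physical activity patterns and miRNA expression profiles".

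The article does not say that all miRNAs are brought to a common scale before the PCA. It does not say whether the PCA uses the covariance or the correlation matrix.

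**The concern.** qPCR expression is multiplicative, so the log scale suits every miRNA in the panel whether or not its raw distribution passes a normality check. Under the stated rule, each miRNA's scale depends on how skewed it happens to look in the sample. Mildly variable miRNAs tend to pass and stay raw, while more variable ones are logged.

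A PCA that seeks maximum variance depends on the units of its inputs unless these are standardised. An abundant miRNA left raw can have a numerical variance far above that of the logged ones. The first component may then describe that one miRNA rather than a pattern shared across the panel. At stake is how the miRNA components are interpreted, and any correlation of diet and activity with expression profiles built from them.

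**Working it through.** The article states no figure for the transformation or the PCA, so there is none to reproduce. The check asks whether the rule can produce mixed scales, and what that does to the first component.

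**Inputs from the article.** "A total sample size of 225 women per ethnic group, consisting of 75 per profile group", hence n = 225 per ethnic group; n = 675 in total (Abstract, Methods/Design); significance at 0.05.

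**Assumed inputs, not in the article.** 10 lognormal miRNAs with one shared factor and a pairwise log-scale correlation of 0.4. Log-SDs and abundances are as given below. Normality is decided by test alone, because plots cannot be simulated.

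**Step 1. Can scales be mixed?** Share of simulated lognormal variables that pass at 0.05 and stay raw (plain Kolmogorov-Smirnov / Lilliefors version):

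| Log-SD | n = 225 | n = 675 |
|---|---|---|
| 0.15 | 1.00 / 0.66 | 0.85 / 0.23 |
| 0.3 | 0.74 / 0.13 | 0.02 / 0.00 |
| 0.5 | 0.05 / 0.00 | 0.00 / 0.00 |

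A panel with log-SDs from 0.15 to 0.8 was mixed in 82–100% of runs at n = 225 and in 14–96% at n = 675. With every log-SD at 0.6 it was mixed in 0–4%. Mixing is therefore plausible for a panel that includes mildly variable miRNAs, and unlikely if all are clearly skewed.

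**Step 2. Why units matter.** A lognormal variable with median m and log-SD s has raw variance m² · exp(s²) · (exp(s²) − 1). Its variance on the natural-log scale is s².

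- For s = 0.15, exp(s²) · (exp(s²) − 1) = 1.0228 × 0.02276 = 0.0233.
- With m = 50, the raw variance is 2500 × 0.0233 = 58.2. The logged variance is 0.0225.
- Suppose the other nine miRNAs are logged, with log-SDs 0.8, 0.7, 0.6, 0.5, 0.4, 0.35, 0.3, 0.25 and 0.2. Their variances sum to 2.215.
- Left raw, the one miRNA holds 58.2 / (58.2 + 2.215) = 96% of the total variance. Logged, it holds 0.0225 / 2.2375 = 1%.
- With m = 1, its raw variance is 0.0233 against 0.0225 logged, and there is almost no effect.

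**Step 3. Effect of the rule alone on the first component.** Mean absolute correlation with the shared factor. The rule is applied with the Lilliefors test, and each comparison keeps the PCA matrix fixed:

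| Setting | Covariance, all logged | Covariance, stated rule |
|---|---|---|
| n = 225, ln-SD 0.1–0.6, abundance SD 3 ln units | 0.90 | 0.81 |
| n = 225, same, abundance SD 1 | 0.90 | 0.87 |
| n = 225, same, equal abundance | 0.90 | 0.90 |
| n = 675, ln-SD 0.1–0.6, abundance SD 3 | 0.90 | 0.87 |

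With ln-SD 0.3–1.0, under 1% of miRNAs stay raw and the loss is below 0.01. With the correlation matrix the value is 0.93 whether all miRNAs are logged or the rule is applied. In the first setting about 85% of data sets were mixed. Repeat runs differ by about 0.01.

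**Step 4. A less favourable arrangement.** Here the least variable miRNAs are the most abundant (levels 0.1 to 50, log-SD falling from 0.8 to 0.15). At n = 225 with covariance PCA, the correlation falls from 0.87 to 0.68–0.70, and the largest squared loading on the first component rises from 0.38 to 0.88–0.89. With correlation PCA nothing changes (0.93 and 0.12 either way).

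**The case against.** The strongest reply is that the harm needs an unstandardised PCA, which the article nowhere specifies. A condensed article may leave the choice of matrix to the full plan, and if the variables are standardised the effect disappears. This stands, and the missing matrix is not itself the finding. What remains is the conditional rule, which the article does state and which has no written safeguard.

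The rule is also less mechanical than a bare p-value. The miRNA sentence does not say that the decision is made for each miRNA, and plots are examined as well as the test. That stands too, although the general rule takes the variable as its unit, so a miRNA-by-miRNA decision is the natural reading.

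A reader might infer more than the document supports:

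- **That scale does drive the components.** It can, under the conditions above. The article does not show that they hold.
- **That a primary result is compromised.** miRNA expression is among the primary outcomes listed in Background, but the ANOVA and logistic analyses are described in terms of miRNA levels. Nothing feeds component scores into them. The correlations of diet and activity with miRNA profiles match a secondary outcome.
- **That scores from 225 women and from 675 would not be comparable because of the rule.** No PCA is planned both by ethnic group and pooled. Separately fitted PCAs have different loadings in any case, even with every miRNA logged.
- **That the whole gap from 0.81 to 0.93 belongs to the rule.** That comparison changes the scale and the matrix together. Of the 0.12, 0.90 − 0.81 = 0.09 comes from the rule and 0.93 − 0.90 = 0.03 from standardising.

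**Conclusion.** The concern holds as a minor, conditional one. The stated rule allows raw and logged miRNAs to enter the same PCA. Distortion follows only if the PCA is unstandardised and the unlogged miRNAs have large raw variance.

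Under the illustrative inputs the rule's own cost at n = 225 is a fall from about 0.90 to 0.81 when abundance varies widely (an SD of 3 ln units, about 20-fold per SD). It is about 0.03 when the SD is 1, and larger in the deliberately adverse arrangement. It is nil with equal abundance or a correlation matrix, and negligible with clearly skewed miRNAs. The number of miRNAs, their abundances, their SDs and the correlation between them are all assumptions, so these figures show a mechanism and a range. They do not predict this study's result.

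**What to change.** State in advance that every miRNA is analysed on one log2 scale after normalisation, whatever the normality check shows, and that the PCA is run on the correlation matrix (standardised variables). Normality checks can stay as a description of the data, but should not decide the scale of individual miRNAs.

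The cost is a sentence or two of wording and trivial analysis work, with no new data or assays. If all miRNAs would have been logged anyway, the log-scale part changes nothing. If the full plan already standardises, one confirming sentence settles the PCA part.

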#### Dietary intake data

A 220-item self-administered semi-quantitative food frequency questionnaire (FFQ) is used. The FFQ was adapted from the validated FFQ used in the Adult National Nutrition survey in NZ (Ministry of Health NZ 1997). Changes include an expanded food list to include currently consumed/available foods, additional questions relating specifically to fast food and snack food intakes, changes to the order of questions to improve continuity between questions. The food intake data will be processed using the Foodworks7 (Xyris Software (Australia) Pty Ltd, Queensland, Australia) dietary analysis database utilising FOODfiles 2010 (developed by the NZ Institute for Plant & Food Research and the NZ Ministry of Health) as the reference food composition table for NZ. Dietary quality and variety of the whole diet will be assessed, including nutritional adequacy and usual intake patterns and adherence to NZ dietary guidelines (Wirt and Collins 2009; Kant and Graubard 2005; Ibiebele et al. 2009). The frequency and patterns of intake of various nutrient-rich/poor dietary components and dietary factors that may affect fat deposition/obesity (e.g. sugar/fat-rich foods, fast foods, etc.) and related habits will be investigated. Foods from the FFQ will be grouped accordingly and factor analysis will be used to determine dietary pattern scores (McNaughton 2011; Mishra et al. 2010). Dietary variety will be assessed using dietary diversity scores and food variety scores to explore the variety of nutritious and non-nutritious foods (Ruel 2003; Murphy et al. 2006). Eating habits, meal patterns and food choices are explored using a self-developed and validated (during the current study) questionnaire, providing descriptive data of the women’s dietary practices.

Dietary behaviour is assessed using the validated TFEQ (Stunkard and Messick 1985; Bond et al. 2001) to measure three eating behaviour traits. The three factors are cognitive dietary restraint (Restraint), disinhibition of control (Disinhibition) and susceptibility to hunger (Hunger) by calculating scores for the dimensions and their sub-categories.

